An open-label, parallel cluster randomised trial will be conducted from October 2023 to March 2025, with villages as the unit of randomisation into the intervention and control arm with a 1:1 allocation. Twelve villages in the Udupi district will be considered clusters in the sampling frame and eligible for randomisation. Six villages each will be allocated to either an intervention or control group, with 118 participants in each group. Randomisation will be performed by an independent biostatistics faculty using a block randomisation method (block size = 4). Allocation will be concealed using opaque, sealed envelopes to minimise selection bias. People diagnosed with hypertension within these clusters will be the targeted population. The eligibility criteria for the clusters include a hypertensive population strength ≥ 10. If a cluster fails to have the prescribed strength, it will be clubbed with an adjacent cluster to achieve the required number. For the individual participants, the eligibility criteria would be people diagnosed with primary hypertension and on medical management (ICD 10 code: I10) for the last 5 years, of either gender, between the ages of 18 and 60 years, who will be able to comprehend health messages in English or Kannada and have access to Android-based smartphones with internet connectivity. The Android platform requirement aligns with the prevalent smartphone ecosystem in the region, where Android devices account for over 90% of the market share among our target demographic, ensuring maximum study feasibility and real-world applicability. We will be excluding people undergoing any other structured behaviour change intervention who are dependent on self-care. Participants currently engaged in regular self-monitoring of blood pressure (defined as measuring BP ≥4 times per week for the past 3 months) will be eligible for inclusion. Still, they will be stratified during randomisation to ensure balanced distribution across intervention and control groups. This approach acknowledges that existing self-monitoring behaviour may influence intervention effectiveness while maintaining the study’s external validity.

The sample size was calculated based on the primary outcome of mean systolic blood pressure reduction, using the formula for cluster randomised trials:

$$n=\left[{\left(z_{\alpha /2}+z_{1-\beta }\right)}^{2},\left\{\left(\sigma_{1}^{2}+\sigma_{2}^{2}\right),/,\delta^{2}\right\}\right]\left[1+\left(m-1\right)\rho \right]$$

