Where n = number of subjects per arm, δ = effect size, σ = standard deviation, m = cluster size, ρ = intraclass correlation coefficient.

Based on systematic review evidence demonstrating that comprehensive mHealth interventions (combining self-monitoring, medication reminders, and lifestyle support) achieve systolic BP reductions of 4-6 mmHg compared to usual care (
Mekonnen et al., 2022;
Chandrasekhar et al., 2021), we anticipate a conservative effect size of 5 mmHg reduction in systolic BP. Assuming a baseline systolic BP of 145 ± 15 mmHg in our population (
Kumar et al., 2020), a five mmHg reduction represents a clinically meaningful 3.4% decrease. With 90% power, 5% significance level (two-sided), design effect of 1.45 (ICC = 0.05), and accounting for 15% attrition, the required sample size is 118 participants per arm distributed across 12 clusters of approximately 20 participants each (total n = 236). A sensitivity analysis confirms adequate power (>80%) to detect systolic BP reductions as small as 3.5 mmHg, ensuring the study can identify clinically meaningful effects consistent with published mHealth intervention studies.

Randomization will be carried out at the cluster level i.e. the villages would be the units of randomization. The entire process of randomization will be carried out by non-participating biostatistics faculty. Sequence generation will be done according to the block technique, with a block size of 4 for 2 allocation categories: ‘A’ for the new intervention and ‘B’ for the standard intervention, yielding 6 different combinations or sequences. Allocation concealment will be achieved through coded opaque sealed envelopes. Thereafter, the interventions will be allocated to the recruited clusters by the investigators strictly according to the sequence of the block. Each of the 3 steps of randomization, namely, sequence generation, allocation concealment, and implementation will be carried out by an independent faculty.

For the participants in the intervention group, the mHealth application will be installed on their smartphones, and the required data will be entered by the primary investigator. A demo of the application features will be provided. Participants from the intervention group will also be given automated BP apparatus. Under established clinical guidelines, participants will receive comprehensive blood pressure measurement training (
Williams et al., 2018;

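### Stratifying individual self-monitors at randomisation cannot be done when whole villages are allocated, so the promised balance is not ensured

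*Protocol article*

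**What the plan says.** All of the relevant text on allocation is in the protocol article, Methods, Phase 3.

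- **The trait.** It belongs to the individual: "Participants currently engaged in regular self-monitoring of blood pressure (defined as measuring BP ≥4 times per week for the past 3 months". Such people are eligible.
- **The promise.** "Still, they will be stratified during randomisation to ensure balanced distribution across intervention and control groups". The article gives as its reason that existing self-monitoring may alter how well the intervention works.
- **The unit of allocation.** The trial is set up "with villages as the unit of randomisation into the intervention and control arm with a 1:1 allocation". This is repeated later: "Randomization will be carried out at the cluster level i.e. the villages would be the units of randomization".
- **The numbers.** "Twelve villages in the Udupi district will be considered clusters in the sampling frame and eligible for randomisation", and "Six villages each will be allocated to either an intervention or control group, with 118 participants in each group".
- **The sequence.** "Sequence generation will be done according to the block technique, with a block size of 4 for 2 allocation categories", giving six possible sequences, applied to the recruited clusters in block order. No stratum is named.

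Under Individual-level analysis, the hierarchical model adjusts for confounders. Four are named: age, gender, baseline blood pressure and medication adherence. Prior self-monitoring is not among them.

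**The concern.** Stratified randomisation balances a factor by running a separate allocation list within each level of it. The units in a list must therefore carry the factor. Here the units are villages and the factor is a personal habit. A village will normally hold both self-monitors and others, and all of them receive the same arm.

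The point matters because home measurement is a central part of the intervention, and the article itself names prior self-monitoring as a possible modifier of its effect. The article offers stratification as its safeguard, and the allocation it describes cannot supply that safeguard. A reader of the trial report would be told that a prognostic factor was balanced by design when it was left to chance across 12 units.

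**Working it through.** **1. What the described scheme is.** A block of 4 with two arms has C(4,2) = 6 sequences, which reproduces the article's count. Twelve villages make 12/4 = 3 complete blocks and exactly 6:6. This fits one unstratified list.

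**2. Could it be a stratified list of villages?** With two village strata, blocks of 4 fill completely only for a 4/8 split. In simulation, strata of 6/6 or 5/7 leave incomplete blocks and give 6:6 in only about 50% of runs. A village-level version is possible, but it needs each village's share of self-monitors before allocation and a block size that suits the strata. The article describes neither.

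**3. What individual stratification would have delivered.** With individuals allocated in blocks of 4, the self-monitor stratum could differ by at most 2 people between arms: 2/118 = 1.7 percentage points. That is the kind of balance the sentence implies.

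**4. What the village allocation delivers.**

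Inputs from the article: 118 per arm, about 20 participants per village, ICC 0.05. Assumptions: prevalence p of self-monitoring from 10% to 30%, and that the ICC, given for the sample size on systolic pressure, also applies to self-monitoring.

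Design effect = 1 + (20 − 1) × 0.05 = 1.95. The article states 1.45, which corresponds to 10 per village (1 + 9 × 0.05), so both are shown.

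95% range of the between-arm difference = ±1.96 × √[2p(1 − p)/118 × design effect]

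| p | design effect 1.95 | design effect 1.45 |
|---|---|---|
| 0.10 | ±10.7 points | ±9.2 points |
| 0.20 | ±14.3 points | ±12.3 points |
| 0.30 | ±16.3 points | ±14.1 points |

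**5. Check by simulation.** The setting was 12 villages of 20, a beta-binomial share of self-monitors, villages allocated in blocks of 4, and 100,000 runs per setting. At ICC 0.05 the SD of the difference is 5.4, 7.2 and 8.3 points for p = 0.10, 0.20 and 0.30. Multiplied by 1.96, these give 10.6, 14.1 and 16.3 points, in agreement with the formula. Over ICC 0 to 0.20 and p from 0.10 to 0.30, the SD runs from 3.9 to 13.0 points, and the chance of a gap of 10 points or more runs from 1% to 46%.

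**6. What a village-level scheme could achieve.** If the villages are ranked by their baseline share and blocked in fours, the SD falls to 2.0 to 6.0 points and the chance of a 10-point gap to 0% to 11%. At p = 0.20 and ICC 0.10, that chance falls from 27% to 3%.

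**The case against.** The best defence is that the sentence states an aim, that a condensed article need not give the mechanism, and that villages can be stratified on their share of self-monitors. The last part is right: balance can be pursued at village level, and it may also arise by chance. The defence still does not rescue the text. The sentence is about participants, the randomisation is described twice without any village-level measure, and no fuller document can make a personal trait a stratum of a village allocation.

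Several stronger readings are tempting, but the documents do not support them.

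- *The arms will be unbalanced.* They may be balanced by luck; the design simply does not ensure it.
- *Individuals will be randomised within villages.* The article fixes villages as the units and describes no individual allocation step.
- *The analysis will leave self-monitoring unadjusted because the authors think randomisation handles it.* The covariate list is introduced as examples, unnamed subgroup analyses are planned, and no motive is stated.
- *The treatment effect will be biased by about 0.5 mmHg.* This multiplies 0.143 by the abstract's 3.2 mmHg (0.46 mmHg). That figure is for self-monitoring and self-management together. The Introduction gives 2 to 8 mmHg for self-monitoring, or about 0.3 to 1.1 mmHg. The standard error of the arm difference on the same inputs is 15 × √(2/118 × 1.95) = 2.7 mmHg, so 0.46 is about 17% of one standard error and 1.1 about 42%. Adjustment for baseline pressure would absorb much of a baseline shift. Chance imbalance under valid cluster randomisation is not bias, and a cluster-adjusted interval already allows for it.
- *Self-monitors dilute the contrast because of this flaw.* Any dilution follows from making them eligible and would remain under perfect balance.

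**Conclusion.** The contradiction stands. The article claims a stratification that its own allocation cannot carry out, and the balance it promises on prior self-monitoring is not ensured. With prevalence assumed at 10% to 30% and an assumed ICC of 0.05 for self-monitoring, the 95% range of the chance difference is about ±11 to ±16 points, or ±9 to ±14 with the article's own design effect. The consequence is mainly lost precision and an incorrect statement about covariate balance. The validity of the primary comparison is not at stake, and no defensible mmHg figure for the effect on the result can be drawn from the documents.

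**What to change.** Withdraw the participant-level stratification sentence. Record baseline self-monitoring status, by the article's definition, for every participant in both arms. Prespecify it as a participant-level covariate in the hierarchical model already planned, and as a named subgroup.

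Alternatively, if status can be established before allocation, replace the sentence with stratified or constrained randomisation of the 12 villages on their share of self-monitors. State how that share is obtained and choose a block size that fits the strata. The covariate is worth keeping in that case too.

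If allocation has already taken place, report what was actually done. The article does not settle this: Phase 3 and Study status put the start of the trial in October 2023, while the Phase 2 Development text puts it in October 2025.

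The cost is a change of wording, one baseline item and one model parameter. The baseline item may be new, since the baseline measurements listed in Phase 3 do not mention self-monitoring status. The village-level option also needs a count in each village before allocation.

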## Abstract

**Background:**

Hypertension is a significant risk factor for cardiovascular disease, contributing to global mortality and disability. Approximately 30% of Indian adults are diagnosed with hypertension. Evidence supports that self-monitoring and blood pressure self-management can lower systolic BP by an average of 3.2 mmHg. mHealth applications facilitate remote monitoring and self-management, yet existing applications in India lack customisation for user needs, limiting their usability. This study aims to develop and evaluate a novel, user-friendly mHealth application tailored to hypertensive individuals.

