Whelton et al., 2018). The orientation protocol will include: (1) timing specifications requiring BP measurement twice daily (morning: 6-10 AM, evening: 6-10 PM) with at least 12 hours between readings; (2) standardised measurement technique involving three consecutive readings taken 1-2 minutes apart, with the first reading discarded and the mean of the second and third readings recorded; (3) pre-measurement requirements including 5 minutes of quiet rest, avoiding caffeine/exercise 30 minutes prior, proper cuff placement directly on skin (not over clothing), and maintaining feet flat on floor with back supported; (4) technical specifications ensuring appropriate cuff size selection and proper arm positioning at heart level; and (5) data entry protocols for recording measurements in the mHealth application immediately after each session. Participants will demonstrate competency in the BP measurement technique before the study commences, with refresher training provided at monthly follow-up contacts. The control group will receive standard care which includes advice to adhere to their prescribed medication and lead an active lifestyle. Baseline measurements like blood pressure, knowledge and practice of management of blood pressure, self-efficacy, and health status will be obtained from the recruited participants in both groups. Blood pressure will be measured with an electronic BP apparatus ([name] BP monitor-118), which will be calibrated periodically. Knowledge and practice will be assessed using a hypertension fact questionnaire. Self-efficacy using Medication Adherence Self-Efficacy Scale (MASES) and Self-Efficacy for Managing Chronic Disease 6-item Scale will be assessed and health status using SF-36 questionnaire will be assessed for pre and post-test (
Fernandez et al., 2008;
Lorig et al., 2001;
Ware & Gandek, 1998). For any reason, if the participant is unable to use the application, we will be discontinuing the intervention regimen for that participant. Regular phone calls will be made to remind them to use the application and to track their BP. The participants will be allowed to withdraw from the study at any given time as per their decision. The consort flowchart of the phase 3 is shown in
Figure 4.

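### The 5 mmHg target is the midpoint of its cited range, not a conservative choice, and the power stated at 5 and at 3.5 mmHg is neither attainable with 118 per arm nor mutually consistent

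*Protocol article*

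**What the plan says.** All of this is in the Protocol article, Methods, Phase 3.

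- **Evidence and target.** Comprehensive mHealth packages are said to "achieve systolic BP reductions of 4-6 mmHg compared to usual care". From this the plan concludes: "we anticipate a conservative effect size of 5 mmHg reduction in systolic BP".
- **Variability.** "Assuming a baseline systolic BP of 145 ± 15 mmHg in our population".
- **Design inputs.** "With 90% power, 5% significance level (two-sided), design effect of 1.45 (ICC = 0.05), and accounting for 15% attrition".
- **Result.** "the required sample size is 118 participants per arm distributed across 12 clusters of approximately 20 participants each (total n = 236").
- **Smaller effects.** The paragraph closes by saying that a sensitivity analysis confirms power above 80% for a systolic reduction as small as 3.5 mmHg.
- **Who may enter.** "Participants currently engaged in regular self-monitoring of blood pressure (defined as measuring BP ≥4 times per week for the past 3 months) will be eligible". The plan intends to balance these people across arms and concedes that their habit may affect how well the intervention works. The sample-size paragraph makes no allowance for them.
- **Comparator.** "The control group will receive standard care which includes advice to adhere to their prescribed medication and lead an active lifestyle".

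**The concern.** A conservative planning effect sits at or below the low end of the supporting evidence. Here the evidence runs from 4 to 6 mmHg and the plan takes the middle. The label tells readers that there is a margin, when a true effect at the bottom of the plan's own range would be smaller than the one planned for.

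That would matter less if the closing statement about 3.5 mmHg were right, because power above 80% there would cover 4 mmHg as well. So the claim has to be tested, together with the 90% at 5 mmHg on which it rests. If both fail, a null result would be reported as a well-powered negative against a cautious target, although the trial had less than an even chance of detecting even the midpoint effect.

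**Working it through.** **Inputs (all from the sample-size paragraph unless noted).** SD 15 mmHg in both arms; ICC 0.05; stated design effect 1.45; two-sided 5%; 90% power; 15% attrition; 118 per arm; about 20 per village; six villages per arm (Phase 3 design paragraph).

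**1. Position of 5 mmHg.** (4 + 6)/2 = 5, the exact midpoint.

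**2. Attempt to reproduce 118 per arm.** With the plan's own formula:
- (1.960 + 1.282)² × (15² + 15²)/5² = 10.507 × 18 = 189.1 per arm before inflation
- × 1.45 = 274.2
- ÷ 0.85 = 322.6, so 323 per arm

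The figure of 118 does not come out. Using 80% power, a one-sided test, no clustering, or attrition added as × 1.15 does not give 118 either.

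**3. Design effect.** 1 + (m − 1) × 0.05 equals 1.45 at m = 10. At the stated m of about 20 it is 1 + 19 × 0.05 = 1.95. With 118/6 = 19.67 per village it is 1.933. Using 1.95 in step 2 gives 189.1 × 1.95/0.85 = 433.9, so 434 per arm.

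**4. Power of the fixed design, no attrition.**
- SE = √(2 × 15² × 1.933/118) = 2.715 mmHg
- Power ≈ Φ(d/SE − 1.96)
- The t version uses a noncentral t with 12 − 2 = 10 df.

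| True difference d | d/SE | Normal | t, 10 df | Plan states |
|---|---|---|---|---|
| 5 mmHg | 1.841 | 45% | 38% | 90% |
| 4 mmHg | 1.473 | 31% | 27% | none given |
| 3.5 mmHg | 1.289 | 25% | 21% | above 80% |

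**5. After 15% attrition.** 118 × 0.85 = 100.3 per arm. The design effect is 1.95 if kept at 20 per village, or 1 + (16.72 − 1) × 0.05 = 1.79 if villages shrink with attrition. Normal-approximation power is 39-42% at 5 mmHg, 27-29% at 4 and 22-24% at 3.5.

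Even with the plan's own 1.45, power after attrition is 50%, 35% and 28%.

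**6. Do the two stated powers agree with each other?** If power is 90% at 5 mmHg, then 5/SE = 3.2415 and power at d is Φ(3.2415 × d/5 − 1.96).
- d = 4: Φ(0.633) = 74%
- d = 3.5: Φ(0.309) = 62%

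In the other direction, 80% at 3.5 mmHg implies Φ((1.960 + 0.842) × 5/3.5 − 1.96), about 98% at 5 mmHg. SD, ICC and sample size cancel here, so the conflict does not depend on any of them.

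**The case against.** **Powering on a midpoint is ordinary practice.** That is so, and nothing here says 5 mmHg is an improper target. Only the label is wrong.

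**A reader might infer that 5 mmHg is too optimistic for this trial**, because established self-monitors may enter both arms and the abstract says "self-monitoring and blood pressure self-management can lower systolic BP by an average of 3.2 mmHg". The document does not establish this.
- The cited 4-6 mmHg and this control arm share the same type of comparator, usual care. Whether the usual-care groups in the cited reviews already contained self-monitors cannot be seen; if they did, the dilution is already in the range.
- The 3.2 mmHg figure is for self-monitoring and self-management, while 4-6 mmHg is for packages that add medication reminders and lifestyle support. A larger effect for a fuller package is no contradiction.
- The share of self-monitors is not given, nor how much benefit each would forgo. Purely as illustration, take shares of 10%, 20% and 30% and let each lose the full 3.2 mmHg: 5 − 0.1 × 3.2 = 4.68, then 4.36 and 4.04. All three stay inside the cited range. Full subtraction is itself doubtful, since the app arm adds training, twice-daily structured readings and monthly refreshers.

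What stands is that balancing self-monitors across arms would not restore a diluted contrast, so the possibility deserves a sentence.

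**The SD of 15 is a baseline SD, and the hierarchical model adjusts for baseline blood pressure.** The residual SD would be smaller. But for 118 per arm to give 90% at 5 mmHg after attrition, it would have to be about 9.1 (design effect 1.45) or 7.8 (1.95). If adjustment acts as 15 × √(1 − r²), that needs a baseline-to-follow-up correlation of √(1 − (9.07/15)²) = 0.80 or √(1 − (7.82/15)²) = 0.85. The plan states neither, and its formula uses the unadjusted SD. Nor would this reconcile 90% at 5 mmHg with more than 80% at 3.5.

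**Conclusion.** The point holds in three parts.

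1. Calling 5 mmHg conservative is wrong on the face of the sentence that says it.
2. The stated powers are not delivered. On the plan's inputs, power before attrition is about 45% rather than 90% at 5 mmHg, about 25% rather than above 80% at 3.5 mmHg, and about 31% at the lower end of the cited range.
3. The two claims are incompatible with each other under any common SD and design effect, unless the design has about 98% power at 5 mmHg, which the plan does not claim.

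Parts 1 and 3 need no assumption beyond the text and the normal approximation. Part 2 rests on SD 15, ICC 0.05 and about 20 per village, all stated by the plan; a well-supported smaller residual SD would raise the figures.

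The shortfall comes mainly from the sizing arithmetic and the design effect. Moving from 5 to 4 mmHg would cost a true 90% design 16 points (90% to 74%), but 118 per arm is not such a design. A loss of power from established self-monitors is not demonstrated.

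**What to change.** In the sample-size paragraph:

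- Delete the word conservative and describe 5 mmHg as the midpoint of the cited 4-6 mmHg range against usual care.
- Replace the 90% statement and the 3.5 mmHg sensitivity statement with the recomputed power of the fixed 236-participant design at 5, 4 and 3.5 mmHg. Use the design effect for about 20 per village (1.95), allow for 15% attrition, and preferably use a t reference with 10 df. If a baseline-adjusted SD is used instead, state it and its source.
- Add one sentence that established self-monitors may enter both arms, that this could reduce the contrast, and that the size is unknown until their baseline share is observed.
- Commit to reading any null result against these figures and its confidence interval, not as a 90%-powered negative.

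The cost is a rewording, a short recalculation and a less favourable stated power. This point requires no change to eligibility or sample size. Whether to enlarge the trial, given that the plan's formula asks for 323 or 434 per arm, is a separate decision for the sponsor.

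### The stated power of more than 80% at 3.5 mmHg does not follow from the plan's inputs and conflicts with its own 90% at 5 mmHg

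*Protocol article*

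**What the plan says.** All the relevant text is in the Protocol article. In Methods, Phase 3, the plan gives the standard formula for a cluster-randomised comparison of two means, with inflation factor 1 + (m − 1)ρ. On the effect it says "we anticipate a conservative effect size of 5 mmHg reduction in systolic BP", after citing reductions of 4-6 mmHg for comprehensive mHealth interventions. On variability: "Assuming a baseline systolic BP of 145 ± 15 mmHg in our population". On error rates and clustering: "With 90% power, 5% significance level (two-sided), design effect of 1.45 (ICC = 0.05"), with 15% attrition. The outcome is that "the required sample size is 118 participants per arm distributed across 12 clusters of approximately 20 participants each (total n = 236").

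The next sentence is the one at issue: "A sensitivity analysis confirms adequate power (>80%) to detect systolic BP reductions as small as 3.5 mmHg". It gives no separate SD, ICC, design effect, sample size or baseline correlation for that sensitivity analysis.

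Elsewhere, the Abstract (Background) says self-monitoring and self-management "can lower systolic BP by an average of 3.2 mmHg". The Individual-level analysis section lists baseline blood pressure among the adjustment variables.

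**The concern.** Power falls quickly as the effect shrinks. A design set at 90% for 5 mmHg cannot stay above 80% when the effect is cut by 30%, unless something else in the calculation changes, and the plan names no such change. The 3.5 mmHg statement also looks far out of reach for 118 per arm with an SD of 15 and 12 villages.

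What is at stake is how the trial's sensitivity is understood. The sentence ends by assuring readers that the study can identify clinically meaningful effects in line with published mHealth studies. Funders, ethics reviewers and later readers of the results will take that as a property of the design. Calling 5 mmHg conservative adds to the reassurance.

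**Working it through.** **Inputs.** From Methods, Phase 3: two-sided 5% level, 90% power, difference 5 mmHg, SD 15, ICC 0.05, printed design effect (DE) 1.45, about 20 participants per village, 6 villages and 118 participants per arm, 15% attrition. Completers: 118 × 0.85 = 100.3 per arm. ICC 0.05 with 20 per village gives DE = 1 + 19 × 0.05 = 1.95; the printed 1.45 corresponds to 10 per village. Both values are carried below.

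**Step 1. Do the two power statements agree on the same inputs?** Let SE be the standard error of the difference. Power of 90% at 5 mmHg means 5/SE = 1.960 + 1.282 = 3.242. At 3.5 mmHg the ratio is 0.7 × 3.242 = 2.269.

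- Power at 3.5 mmHg = Φ(2.269 − 1.960) = Φ(0.309) = 62%.
- If 90% refers to completers after 15% loss and nobody is lost, the ratio is 2.269/√0.85 = 2.461, and power = Φ(0.501) = 69%.
- Difference at which power is 80%: 5 × (1.960 + 0.842)/3.242 = 4.3 mmHg.
- Conversely, 80% at 3.5 mmHg implies Φ(2.802/0.7 − 1.960) = 98% at 5 mmHg, not 90%.

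SD, ICC and N cancel here, provided the same values apply to both statements.

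**Step 2. Can the stated figure be reproduced from the printed inputs?** SE = 15 × √(2 × DE/n), and power = Φ(δ/SE − 1.960). The t column uses a noncentral t with 10 df (12 villages, two arms).

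| δ (mmHg) | DE | n per arm | SE | Power, normal | Power, t on 10 df |
|---|---|---|---|---|---|
| 3.5 | 1.45 | 118 | 2.35 | 32% | 27% |
| 3.5 | 1.45 | 100.3 | 2.55 | 28% | 24% |
| 3.5 | 1.95 | 118 | 2.73 | 25% | 21% |
| 3.5 | 1.95 | 100.3 | 2.96 | 22% | 19% |
| 4 | 1.45 | 118 | 2.35 | 40% | 34% |
| 4 | 1.45 | 100.3 | 2.55 | 35% | 29% |
| 4 | 1.95 | 118 | 2.73 | 31% | 26% |
| 4 | 1.95 | 100.3 | 2.96 | 27% | 23% |

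With clustering ignored (DE = 1) and all 118 analysed, power at 3.5 mmHg is 43%, or 56% with a one-sided test. No variant reaches 80%.

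**Step 3. What would make the statement true at 118 per arm?** The required SD is (3.5/2.802) × √(n/(2 × DE)), which is 8.0 mmHg at DE 1.45 and 6.9 mmHg at DE 1.95, about half the only SD given. If baseline adjustment is to shrink 15 to those values through 15 × √(1 − r²), the correlation r must be about 0.85 or 0.89. Assumed r of 0.5-0.7 gives 28-55% (DE 1.45-1.95, 100 to 118 per arm).

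**Step 4. Scale of the gap.** For 80% at 3.5 mmHg the unclustered requirement is 2 × (15 × 2.802/3.5)² = 288 per arm. With attrition this becomes 288.3 × 1.45/0.85 = 492, or 288.3 × 1.95/0.85 = about 662 per arm. These hold the design effect fixed, so they presuppose more villages rather than larger ones.

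**The case against.** The best defence is that a sensitivity analysis normally varies its inputs, so the two statements need not share them. They become mutually consistent if the second used an SD about 19% smaller (0.7 × 3.242/2.802 = 0.81). Baseline adjustment with r of about 0.59 would supply that, and the plan does intend to adjust for baseline blood pressure. This stands as a limit on the contradiction: it holds on common inputs, and a reader should not conclude that the two statements are irreconcilable whatever SD or ICC is chosen. It does not rescue the claim. No alternative input is stated, the printed formula has no correlation term, and 118 per arm at SD 15 would need r of about 0.85-0.89.

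Three stronger readings are tempting but unsupported.

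- A single true figure of 20-25% replaces the printed design effect of 1.45 by about 1.95. That mismatch is an error in its own right, so both values should be shown.
- A reader might infer from the 3.2 mmHg in the Abstract that effects of 3-4 mmHg are the likeliest. That figure concerns self-monitoring and self-management, whereas Phase 3 cites 4-6 mmHg for comprehensive mHealth interventions. It is not a like-for-like rebuttal of 5 mmHg.
- The sentence does not say that a null result would exclude 3.5 mmHg. It speaks only of power to detect, and the plan promises 95% confidence intervals, which would show what is excluded.

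It is also fair to say that much of the low absolute power comes from a separate problem: 118 per arm does not follow from the stated inputs. The 5 mmHg target needs 189.1 × 1.45/0.85 = 323 per arm at the printed design effect.

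**Conclusion.** Wrong as written. On common inputs, the plan's 90% at 5 mmHg implies about 62% at 3.5 mmHg, or 69% with no attrition. On the printed SD and sample size, power at 3.5 mmHg is about 19-32%, depending on the design effect (1.45 or 1.95), on whether 118 or about 100 per arm are analysed, and on a normal or 10-df t reference. At 4 mmHg it is about 23-40%.

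The first result rests only on both statements sharing one SD, ICC, sample size and analysis. The second takes SD 15 as the outcome SD, since no other is given, and makes no reduction for baseline adjustment, since no correlation is stated. The wording on 5 mmHg is a smaller point: the midpoint of a cited range is not a conservative choice from it.

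**What to change.** Delete the 3.5 mmHg sentence. Alternatively, replace it with recalculated power for 12 villages and 118 per arm, stating the SD, ICC, design effect, attrition and any baseline correlation used, with a source for that correlation. The design effect must first be reconciled with the ICC and the village size. Describe 5 mmHg as the midpoint of the cited range and drop the word conservative.

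The cost is wording only: this correction alters no procedure, analysis or recruitment target. The one downside is that the stated sensitivity becomes less favourable.
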